### Outcome measures

The primary outcome is global cognitive function, as assessed by both a standard neuropsychological assessment and the MyCQ™, at baseline and 12 weeks after baseline assessment. The standard neuropsychological assessment consists of various tests covering the following domains: executive function (Stroop Colour Word Test [28], category fluency and letter fluency in parallel versions [29]), memory (Rey Auditory Verbal Learning Test in parallel versions [30], Location Learning Test [31]), visual perception (Judgement of Line Orientation in parallel versions [32]), visuoconstruction (Rey-Osterrieth Complex Figure [33, 34]), and language (Boston Naming Test – Short Form). A compound score for overall (global) cognitive function will be calculated as the mean score of all test Z-scores based on the distribution of scores for both groups taken together. Z-scores of tests with higher scores representing worse performance will be inverted before computing the compound scores. By comparing Z-scores across different neuropsychological tests, the neuropsychological profiles of participants can be directly compared to identify the domains that benefitted most from the intervention.

The participants will also perform a monthly web-based online neuropsychological assessment (MyCQ™), which is part of the intervention program. Since the MyCQ™ is integrated in the AquaSnap health game (i.e., the difficulty level of the game automatically adapts according to MyCQ™ performance), it is not an independent measure of treatment effects, and hence the standard neuropsychological test battery is the primary outcome measure.

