### Statistical analysis procedure

Differences between the intervention and control group in global cognitive function (compound score of the neuropsychological test battery) at 12 weeks (primary endpoint) will be compared using independent sample t-tests. In addition, differences between groups in the individual cognitive domains will be tested using multivariate analysis of variance (MANOVA). Change in cognition over time (baseline, 12 weeks, 24 weeks) will be tested using repeated-measures ANOVA. All tests will be two-tailed with alpha set at 0.05. The assumptions of normality and homogeneity of variance will be assessed by inspection of normal probability plots and residual plots. In case assumptions are not met, appropriate data transformations will be used. Secondary outcomes will be presented as means, standard deviations, minimum, maximum, median, lower and upper quartiles. The number of observations and changes from baseline will be presented. Categorical data will be presented in contingency tables as frequencies and percentages. The analyses will be performed on an intention-to-treat basis. A secondary “Per-Protocol” analysis will also be included for the patients who have fully completed the study protocol for the primary endpoint. In order to investigate the effect of ‘missingness’, sensitivity analyses will be performed, including missing data augmentation using multiple imputation by chained equations [45] and maximum likelihood estimation with random effects.

For the main study, interim analysis will be conducted after 40 patients have completed the 12-week cognitive training period, including the corresponding assessments, to find out if the training is particularly beneficial or not. If, after interim analysis, it can be concluded that the training is particularly harmful, we may end the study and analyze the study data. This will only be decided in consultation with the local ethics committee.

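### Comparing Z-scores across tests cannot show which cognitive domains benefitted most, and no planned test asks whether the effect differs between domains

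*Protocol article*

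**What the plan says.** Under Outcome measures, the article lists a battery of eight tests in five domains. Executive function has three (Stroop, category fluency, letter fluency) and memory has two (Rey Auditory Verbal Learning Test, Location Learning Test). Visual perception, visuoconstruction and language have one each. The compound score is "calculated as the mean score of all test Z-scores based on the distribution of scores for both groups taken together". The section then says that with Z-scores compared across tests, "the neuropsychological profiles of participants can be directly compared to identify the domains that benefitted most from the intervention". It gives no formula for a domain score.

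Under Statistical analysis procedure, the primary comparison is a t-test of the compound score at 12 weeks. For the domains, "differences between groups in the individual cognitive domains will be tested using multivariate analysis of variance (MANOVA"). Repeated-measures ANOVA is described for change over the three visits, with no mention of domain as a factor. Under Power and sample size estimate, the trial is sized on the compound score only.

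**The concern.** To say that one domain benefitted more than another is a claim about a difference between two effects. Z-scoring puts the tests in common units, but it attaches no uncertainty to the ordering of the effects.

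The MANOVA does not fill the gap. Its null hypothesis is that the arms do not differ on any of the domains. If the game raised every domain by the same amount, that null would be false and the MANOVA should reject it, yet no domain would have gained more than another. Nor do separate results by domain settle the matter: a significant difference in one domain and a non-significant one in another is not evidence that the two differ.

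What is at stake is a secondary message about where the game works. The primary objective is worded in terms of improvement on targeted domains, so domain-level statements are likely to be prominent in the report, and an ordering produced by sampling variation could be read as a finding.

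**Working it through.** **The plan's own figure.** With d = 0.4, 80% power and two-sided alpha 0.05, the normal approximation gives 2 × (1.96 + 0.8416)² / 0.4² = 98.1, so 99 per arm. The t-based calculation gives 99.08, so 100 per arm and 200 in total, as stated. Allowing for 10% attrition, 200 / 0.9 = 222.2, in line with the stated 222. The sample size reproduces, and it concerns the compound score only.

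**Inputs for the domain check.**
- From the article: 100 evaluable per arm; 3, 2, 1, 1 and 1 tests per domain; Z-scored tests (SD taken as 1 within arm).
- Assumed, because the article gives no correlations: within/between-domain correlation of 0.4/0.2, 0.5/0.3 and 0.6/0.4.
- Domain score: plain mean of its test Z-scores, the same rule as the compound score.

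**Standard errors.** For a mean of k tests with within-domain correlation w, the score SD is √[(1 + (k − 1)w)/k], and the SE of the arm difference is that SD × √(2/100). At w = 0.5:
- executive (k = 3): 0.816 × 0.1414 = 0.115
- memory (k = 2): 0.866 × 0.1414 = 0.122
- one-test domains: 0.141

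If every test gains 0.40, the expected effect is 0.40 in every domain, whatever its number of tests. Only the SE changes.

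**Noise alone.** Simulating the five arm differences with equal benefit in every domain gives an expected top-minus-bottom gap of 0.27, 0.25 and 0.23 SD for the three correlation settings. Against the design effect, 0.23/0.4 = 58% and 0.27/0.4 = 68%.

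**A real difference.** If one domain truly gains 0.1 Z more than the other four, it is ranked first in about 43 to 50% of trials, depending on the domain and the correlations. With no real difference, the average would be 20%.

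**Test count.** Chance of ranking first when every test gains 0.4:

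| How the ranking is made | Executive | Memory | Each one-test domain |
|---|---|---|---|
| Plain mean of Z | about 16% | about 18% | about 22% |
| Domain mean rescaled to SD 1 | 32–40% | 25–27% | 11–14% |
| Domain of the single largest test (0.5/0.3) | 35% | 25% | 13.5% |

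Rescaling favours executive function because it divides the same 0.40 by a smaller SD: 0.40/0.775 = 0.52 at w = 0.4 and 0.40/0.856 = 0.47 at w = 0.6, against 0.40 for a one-test domain.

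**Precision of a between-domain contrast.** For two one-test domains with correlation b, the SE of the difference between their effects is √[2 × 0.02 × (1 − b)]. That is 0.179 at b = 0.2 and 0.155 at b = 0.4. A true difference of 0.1 is therefore only 0.56 to 0.65 standard errors.

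**The case against.** The sentence is permissive and speaks of domains in the plural. It fixes no ranking statistic and does not require a single winner. The article is a condensed account, and the full protocol or SAP may define domain scores and follow-up models. The declared domain analysis is the MANOVA, and the primary endpoint and sample size do not depend on any ranking.

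Most of this stands and limits the weight of the point. The absence of a domain-score formula is not itself a fault here. What remains is an affirmative statement that a direct comparison of Z-scores can identify the domains with most benefit. That is wrong as stated, and the MANOVA answers a different question.

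A reader might go further and infer that the ranking is driven by the number of tests, to the disadvantage of executive function and memory. The documents do not support that. Under plain averaging with equal gains per test, the tilt is small (16% against 22%). Executive function falls to 5–8% only if equal benefit is defined in domain-SD units, which assigns each executive test a smaller gain from the start, while the article works in test Z-scores. Other ways of building the score favour executive function instead. A reader might also take the ranking to be a stated objective. The Objectives section and the Discussion ask whether targeted domains improve, not which improves most.

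**Conclusion.** The point holds as a secondary one. The plan claims that comparing Z-scores can show where benefit was greatest, but nothing described tests whether the effect differs between domains. When all domains benefit equally there is no right answer, so the error would be to report a difference that does not exist. Sampling noise is the main cause: a gap of about 0.23 to 0.27 SD is expected from equal effects, and a true 0.1 Z advantage is ranked first no more than about half the time. The unequal test counts matter less, and their direction depends on the score definition. These figures rest on 100 per arm, test SD 1, plain averaging and assumed correlations of 0.4/0.2 to 0.6/0.4. The primary compound-score comparison is not affected.

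**What to change.** In Outcome measures and Statistical analysis procedure, replace the cross-test comparison with three steps:

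1. Define each domain score in advance on one stated scale, for example the mean of its test Z-scores, which matches the compound score. Rescaling to SD 1 is a choice of metric and should not be presented as neutral.
2. Report the between-arm difference at week 12 for each domain, with a confidence interval.
3. Test the arm-by-domain interaction in one model. State that a domain benefitted more than others only if that test supports it. Otherwise report the five estimates without ranking them.

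The cost is a change of wording and one further model on data already collected. The drawback is modest power for the interaction, so the trial may end without naming a domain that benefitted most.

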### Additional study parameters

#### Non-motor symptoms

Several assessments will be performed at baseline. The Montreal Cognitive Assessment (MoCA) is used to assess global cognition and it is suggested to be more sensitive to cognitive impairment in PD populations in comparison with the Mini Mental State Exam (MMSE) [35]. MoCA includes several neuropsychological items focussing on memory, language, executive function, and visuospatial processing [36]. The Dutch National Adult Reading Task (NART) estimates premorbid intelligence levels. The test is untimed and consists of 50 words with atypical phonemic pronunciation. Each word is presented individually and subjects are asked to read them out loud [37].

Depression will be assessed with the Hamilton Anxiety and Depression Scale (HADS) [38], which has been validated in PD [39]. The Epworth Sleepiness Scale is used to provide a measurement of the subject’s general level of daytime sleepiness [40]. The Cognitive Failure Questionnaire (CFQ) contains 25 questions and provides a self-report evaluation of perception, memory and motor-function in daily life [41]. The Parkinson’s Disease Cognitive Functional Rating Scale (PD-CFR) is a 12-item questionnaire for rating functional abnormalities associated to cognitive impairment in non-demented PD patients [42]. The pre-Rasch-built Overall Disability Scale (pre-R-ODS) can be used to capture functional disability of the patients in a descriptive way [43]. Quality of life will be assessed with the Parkinson Disease Questionnaire (PDQ-39) [44]. The Barratt Impulsiveness Scale 11 (BIS-11) is a 30-item self-report questionnaire that measures impulsive behaviour [45].

#### Motor functioning

The unified Parkinson’s disease rating scale (MDS-UPDRS) part III is used to assess and monitor disability and impairment in PD patients.

#### Compliance

Compliance and attractiveness of the health game will be determined based on the number of dropouts and the cognitive training duration in both groups. Additionally, extended compliance in the intervention group, who continue to play the health game between 12 and 24 weeks from baseline, will be tracked. Comparable studies among both healthy subjects as well as PD patients have found increased cognitive abilities after 6 months follow-up [46, 47] and 1 year follow-up [12]. Based on these studies, we expect to find long term benefits of AquaSnap. Moreover, with a 24 week follow-up measurement, we’re able to test the feasibility of the intervention based on the motivation of the subjects to continue playing AquaSnap.

#### fMRI

MRI imaging will be performed on a 3.0-Tesla unit and in the ON-medication state. Imaging will consist of a neuroradiological protocol (T1-weighted sequences), supplemented with full brain functional imaging (N-back fMRI and resting-state fMRI for functional connectivity imaging). T1 scans will be used to assess macro-structural findings. Volumetric assessment of T1-weighted images will be performed using FreeSurfer software. Task based fMRI will be assessed using SPM and resting state fMRI will be assessed using Melodic. In addition, changes in the resting-state sensorimotor network, including the supplementary motor area, sensorimotor cortex, and secondary somatosensory cortex [19], will be analysed using a robust data-driven approach: independent component analysis (ICA) [48, 49]. Imaging will be performed at the Department of Radiology of the Maastricht University Medical Center. The assessors performing the fMRI baseline and follow-up assessments are blinded for treatment allocation.

### Study activities

Enrolment will take place in the weeks prior to baseline assessment, except for the additional inclusion assessments (see Table 4). The following demographics and general variables are collected at baseline: date of birth, sex, educational level, age at onset, disease duration, and details on Parkinson medication (i.e., drug name, dose, frequency, levodopa equivalence). Details on Parkinson medication will also be collected at both follow-up measurements. Randomization will be performed after the baseline assessment. Primary and additional outcome assessments will be performed at baseline, after 12 and after 24 weeks follow up. The additional fMRI scans will be performed at baseline and after 12 weeks, matching the primary outcome assessments. The intervention group will be required to play the health game from start of the intervention until week 12 for at least 36 sessions of 30 min (three times a week). After week 12, both the intervention as well as the control group will be allowed to continue playing the health game free of choice. All patients will be examined in their on-state.

**Table 4 Tab4:** Study schedule and assessments

	Timepoint →	-*t* _1_	*t* _0_			*t* _1_	*t* _2_
	Visit # →	0	1			2	3
	Week # →	-1 to -3	0	4	8	12	24
ENROLMENT: Screening & inclusion assessments							
Regular clinical intake		X					
Demographics		X					
Inclusion/exclusion		X					
National Adult Reading Task			X				
Montreal Cognitive Assessment			X				
Epworth Sleepiness			X				
Levodopa equivalent dose (LED)			X			X	X
ASSESSMENTS: Primary outcomes							
Standard neuropsychological battery			X			X	X
MyCQ™ assessment			X	X	X	X	X
Additional outcomes							
Motor function (UPDRS part III)			X			X	X
Self-report questionnaires			X			X	X
Parkinson Disease Questionnaire-39			X			X	X
Pre-Rasch-built Overall Disability Scale			X			X	X
fMRI exclusion criteria		X					
fMRI scan			X			X	
INTERVENTIONS							
Randomization			X				
Game playing (36 sessions of 30 min)			X	X	X	*X*	*X*

Only for subset of patients (*n* = 40)

### Data collection and management

All personnel involved in data collection will review the standard operating procedures (SOP) and manuals. Assessors will be certified in Good Clinical Practice (GCP), certified in performing the MDS-UPDRS-III, and trained in assessing the neuropsychological test battery and other assessments by experienced raters. Data will be collected on paper forms and entered into a web-based data entry portal. Questionnaires are completed digitally and are imported automatically in the electronic database, of which a backup will be made daily. A member of the research team will monitor inclusion progress and data collection progress. After completion of the Parkin’Play study, the database will be approved and locked before data-analysis is set in motion.

### Statistical analysis procedure

Differences between the intervention and control group in global cognitive function (compound score of the neuropsychological test battery) at 12 weeks (primary endpoint) will be compared using independent sample t-tests. In addition, differences between groups in the individual cognitive domains will be tested using multivariate analysis of variance (MANOVA). Change in cognition over time (baseline, 12 weeks, 24 weeks) will be tested using repeated-measures ANOVA. All tests will be two-tailed with alpha set at 0.05. The assumptions of normality and homogeneity of variance will be assessed by inspection of normal probability plots and residual plots. In case assumptions are not met, appropriate data transformations will be used. Secondary outcomes will be presented as means, standard deviations, minimum, maximum, median, lower and upper quartiles. The number of observations and changes from baseline will be presented. Categorical data will be presented in contingency tables as frequencies and percentages. The analyses will be performed on an intention-to-treat basis. A secondary “Per-Protocol” analysis will also be included for the patients who have fully completed the study protocol for the primary endpoint. In order to investigate the effect of ‘missingness’, sensitivity analyses will be performed, including missing data augmentation using multiple imputation by chained equations [45] and maximum likelihood estimation with random effects.

For the main study, interim analysis will be conducted after 40 patients have completed the 12-week cognitive training period, including the corresponding assessments, to find out if the training is particularly beneficial or not. If, after interim analysis, it can be concluded that the training is particularly harmful, we may end the study and analyze the study data. This will only be decided in consultation with the local ethics committee.

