The aging brain is thought to retain some degree of plasticity [6], which suggests that older adults may benefit from cognitive training programs. Most studies on the effect of cognitive training programs have been performed in healthy older adults, or in people with cognitive impairment due to vascular pathology or traumatic brain injury. Results showed that these programs could improve multiple domains of cognition [7–9]. So far, only a few cognitive intervention-studies have been conducted in PD patients [10–12]. Some have shown that cognitive training programs improved memory performance [11] and overall cognitive functions [12] after only six weeks of training. Furthermore, cognitive training resulted in a reduced risk of developing PD-MCI at a one-year follow up assessment [12]. Indeed, a recent systematic review by Leung et al. [13] demonstrated a modest effect (g = 0.23, 95 % confidence interval 0.014–0.44, *p* = 0.037) of cognitive training on cognitive function in patients with mild to moderate PD. According to Leung et al. [13], studies in larger samples are needed to examine the abilities of a cognitive training in preventing cognitive decline in PD.

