### Randomization and blinding

After the baseline measurements are performed, participants will be randomly assigned to one of two groups: the Intervention group (IG), or the Control group placed on a waiting list (CG), in a 1:1 ratio. Randomisation (minimisation) will be performed by the Clinical Trial Centre Maastricht (not formally involved in the study or assessments) using the software package ALEA (Formsvision BV). Stratification factors include site location (Maastricht, Nijmegen, or Heerlen) and age group (<60 and > =60 years old). The study is an open-randomised controlled trial, so there will be no blinding for treatment allocation. Nonetheless, all follow-up measurements will be assessed by blinded outcome assessors. Patients will be enrolled by a coordinating investigator, who assigns patients to the intervention groups.

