### Power and sample size estimate

The Parkin’Play study is powered to show a moderate effect of the AquaSnap cognitive training on the standard neuropsychological assessment. A study in healthy older participants compared a brain training program (Brain Age) to a control condition (Tetris gaming) and found an ANCOVA-based effect size of Cohen’s f = 0.39 (eta^2^ = 0.13) on the Trail Making Test, which assesses cognitive flexibility, often reduced in PD [9]. This reflects a moderate-to-large effect size (equivalent of Cohen’s d of 0.78). The present population includes participants aged between 40 and 75 years old, but with PD. Still, we expect a moderate effect size (0.4–0.5). Therefore, the estimated sample size for detecting a difference between the means of the treatment groups on the compound score of standard neuropsychological tests, with a power of 0.8 and a Cohen’s d = 0.4, at an alpha-level of 0.05, for a two-sided test, and an allocation ratio of 1:1 is 200 patients.

Based on previous cognition training and video game clinical trials the attrition rate is estimated at 10 %, which yields an additional 22 patients that should be recruited for participation [9, 11, 50]. This leaves a total of 222 patients that should be recruited.

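### The primary t-test on the 12-week compound score uses neither the baseline score nor the minimisation factors: it is valid and has its stated power, but gives up precision that costs nothing to recover

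*Protocol article*

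**What the plan says.** All places are in the protocol article.

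- **Statistical analysis procedure** names the primary test: compound scores "at 12 weeks (primary endpoint) will be compared using independent sample t-tests". It adds: "All tests will be two-tailed with alpha set at 0.05". Baseline enters only a separate repeated-measures ANOVA over baseline, 12 and 24 weeks. A random-effects likelihood model is listed as a sensitivity analysis for missing data, with no covariates stated.
- **Study activities**: "Primary and additional outcome assessments will be performed at baseline, after 12 and after 24 weeks follow up". Table 4 shows the standard battery at weeks 0, 12 and 24. Under Randomization and blinding, allocation follows the baseline measurements.
- **Randomization and blinding**: allocation is by minimisation. "Stratification factors include site location (Maastricht, Nijmegen, or Heerlen) and age group" (split at 60 years).
- **Outcome measures**: the compound score is the mean of the test Z-scores, standardised on both groups combined. The visit that supplies the reference mean and SD is not stated.
- **Power and sample size estimate**: the calculation is made "with a power of 0.8" and Cohen's "d = 0.4, at an alpha-level of 0.05, for a two-sided test, and an allocation ratio of 1:1 is 200 patients". With 10% attrition this becomes 222 recruited.

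**The concern.** Neuropsychological scores usually vary a good deal between patients in ways that persist from one visit to the next. An unadjusted comparison at 12 weeks leaves all of that variation in the error term, although the plan already measures it in each patient before allocation.

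The design also forces the arms to be similar on site and age group. An analysis that ignores those factors computes its standard error as if the arms had been left free to differ on them.

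What is at stake is the width of the confidence interval and the chance of detecting an effect smaller than planned. The Background section gives a reason to care: it reports that a systematic review of cognitive training in Parkinson's disease "demonstrated a modest effect (g = 0.23", which is below the planning value of 0.4.

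**Working it through.** **1. The plan's own figure.** Inputs from Power and sample size estimate: d = 0.4 (SD = 1), power 0.80, two-sided alpha 0.05, 1:1 allocation.

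- Normal approximation: n per arm = 2(1.960 + 0.8416)² / 0.4² = 2 × 7.849 / 0.16 = 98.1, so 99 per arm (198).
- Exact noncentral t: 100 per arm (200), with power 0.804.
- Attrition: 200 / 0.90 = 222.2, stated as 222.

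The stated 200 and 222 reproduce. The sample size matches the unadjusted t-test.

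**2. Adjustment for baseline.** With correlation r between the baseline and 12-week compound scores, the residual variance is (1 − r²) times the unadjusted variance. The target stays the same raw difference, 0.4 of the unadjusted SD. With 100 per arm:

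- SE = √(2(1 − r²)/100)
- power ≈ Φ(0.4/SE − 1.96)
- detectable d at 80% power = 2.8016 × SE

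The article gives no r, so these values are assumptions. All rows use the normal approximation.

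| Assumed r | Variance left | SE relative to t-test | Power at d = 0.4 | Detectable d | Total N for 80% power |
|---|---|---|---|---|---|
| none (t-test) | 100% | 1.00 | 0.807 (exact t 0.804) | 0.396 | 198 |
| 0.5 | 75% | 0.866 | 0.904 | 0.343 | 148 |
| 0.6 | 64% | 0.800 | 0.942 | 0.317 | 126 |
| 0.7 | 51% | 0.714 | 0.977 | 0.283 | 102 |
| 0.8 | 36% | 0.600 | 0.997 | 0.238 | 72 |
| 0.9 | 19% | 0.436 | >0.999 | 0.173 | 38 |

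Worked line for r = 0.7: SE = √(2 × 0.51/100) = 0.101; 0.4/0.101 − 1.96 = 2.00; Φ(2.00) = 0.977.

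**3. The minimisation factors.** Minimisation on three sites and two age groups was simulated with N = 200 and 4,000 runs per scenario. Assumed, because the article does not give them: a biased coin of 0.8, site shares of 40/35/25%, age shares of 30/70%, and the share of outcome variance that site and age group explain. For comparison, the limit under perfect balance is 2(1 − Φ(1.96/√(1 − R²))).

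| Variance explained (R²) | Type I error, t-test | Type I error, adjusted model | Perfect-balance limit for t-test |
|---|---|---|---|
| 0% | 0.047 | 0.047 | 0.050 |
| 5% | 0.045 | 0.051 | 0.044 |
| 10% | 0.043 | 0.053 | 0.039 |
| 20% | 0.029 | 0.048 | 0.028 |
| 30% | 0.018 | 0.052 | 0.019 |

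The simulation error on a rate near 0.05 is √(0.05 × 0.95/4000) = 0.003, so the 5% and 10% rows differ little from nominal. At 20%, the mean reported standard error is 0.141 and the true SD of the estimate is 0.127. The error runs in one direction: the standard error is too large.

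**4. Whether another planned analysis fills the gap.** The repeated-measures ANOVA is not the primary test. Its 24-week visit comes after the control group has been offered deferred training from week 12, so its overall group-by-time effect does not isolate the 12-week contrast. The random-effects model addresses missing data and names no baseline, site or age term.

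**The case against.** The strongest reply is that nothing here is invalid. Under randomisation the 12-week difference estimates the same treatment effect as a baseline-adjusted one, and chance imbalance at baseline is already part of the t-test's sampling error. The trial has its 80% power at d = 0.4, and its test errs on the conservative side. All of this stands. A reply that the full analysis plan may adjust is weaker, because the article names a specific test that takes no covariates.

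A reader might also draw four stronger conclusions that the article does not support:

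- **That about half the precision is lost.** This needs r near 0.7 (1 − 0.707² = 0.50), and no such figure is given. At r = 0.3 only 9% of the variance would be removed, and power would be 0.84.
- **That the standard error is wrong in a way that threatens the type I error.** It is too large, and the effect is negligible if site and age group explain 5% of the variance or less.
- **That the planning effect is on the wrong scale.** The sample-size section notes that an earlier study in healthy older people "found an ANCOVA-based effect size of" Cohen's f = 0.39, equated to d = 0.78. It then sets that value aside for a different population and computes with 0.4. Converting 0.78 to a raw scale would also need facts about that study that the article does not give.
- **That the trial is underpowered because of g = 0.23.** The article does not state the scale of that g, so no adjusted power is computed from it here.

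**Conclusion.** The point holds as a loss of efficiency and a mild mismatch between design and analysis. It is not an error in sample size, in validity or in type I error control.

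That the test leaves out baseline score, site and age group is certain from the text. How much is lost is not. It rests on an assumed r, and for 0.5 to 0.9 adjustment removes 25% to 81% of the variance. The conservatism from ignoring the minimisation factors rests on how prognostic site and age group are, which is also assumed, and it is small at 10% explained variance or less. The change should be made, because the data are already being collected and the likely gain is material over most of that range. The trial would still be interpretable without it.

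**What to change.** Before database lock, replace the primary t-test with a linear model (ANCOVA) of the 12-week compound score on treatment group, baseline compound score, site and age group. Report the adjusted mean difference with its 95% confidence interval as the primary result. The t-test may stay as a supportive analysis.

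State one common reference for the Z-scores at both visits, for example the pooled baseline mean and SD, so that the covariate and the outcome are on the same scale.

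The cost is a short change to the analysis and outcome sections. No new data and no extra patients are needed, and the sample-size section can stay as it is: 200 evaluable patients suffice for the unadjusted test and remain sufficient for the adjusted one.
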